**Methods:**

Individuals with overweight/obesity who do not habitually consume a MED dietary pattern will complete a 16-week randomized, multi-intervention, semi-controlled feeding study of isocaloric dietary interventions: (1) MED-amplified dietary pattern, containing 500 kcal/day from eight MED target foods: avocado, basil, cherry, chickpea, oat, red bell pepper, walnut, and a protein source (alternating between salmon or unprocessed, lean beef), and (2) habitual/Western dietary pattern, containing 500 kcal/day from six non-MED target foods: cheesecake, chocolate frozen yogurt, refined grain bread, sour cream, white potato, and unprocessed, lean beef. After a 2-week washout, participants complete four, 4-week intervention periods, with biospecimen sampling and outcome assessments at baseline and at intervention weeks 4, 8, 12, and 16. The primary outcome is change in the relative abundance of FSCs from the eight MED target foods in participant biospecimens from baseline to the end of each intervention period. Secondary outcomes include mean change in cardiometabolic health indicators, inflammatory markers, and adipokines. Exploratory outcomes include change in diversity and community composition of the gut microbiota.

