### Objectives {7}

The primary aim of the study is to validate results from metabolomics analyses of foods and biospecimens from a completed MED-style dietary intervention in a prospective feeding trial. Our primary hypothesis is that pre-defined FSCs in participant biospecimens will be responsive to dietary intakes and reproducible within individuals over time, with beef FSCs stable and reproducible within the context of different dietary backgrounds (i.e., the MED and Western dietary patterns). Our secondary aims are to evaluate impacts of incremental changes in diet on cardiometabolic health indicators and microbiome structure and function. Our secondary hypotheses are that a Mediterranean-amplified dietary pattern will lead to improvements in cardiometabolic health indicators and beneficial changes in gut microbiome diversity and community composition over time and compared to a habitual/Western-style dietary pattern.

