### Trial design {8}

This trial is a 16-week randomized, multi-intervention, semi-controlled feeding study of Mediterranean-amplified (mini-MED) and habitual/Western-style (Western) isocaloric dietary interventions containing 500 kcal/day from target foods. Participants are randomized (1:1) to start either the mini-MED or the Western dietary intervention, with subsequent assignment to the other upon completion of the first. Each 4-week intervention (mini-MED and Western) is repeated once. The Western intervention serves as both a washout of the mini-MED foods and a negative control for the postprandial response when the mini-MED foods are not consumed. Within the mini-MED arm, participants are further randomized to first receive salmon (mini-MED salmon) or lean, unprocessed beef (mini-MED beef) as a protein source, with consumption of the alternate protein source in their second mini-MED intervention period (Fig. 1). Outcome measures and biospecimen sampling take place at baseline and intervention weeks 4, 8, 12, and 16, and outcomes will be assessed using an exploratory approach.

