### Assignment of interventions: allocation

#### Sequence generation {16a}

All participants complete the mini-MED and Western dietary interventions twice each for four total intervention periods. Participants are randomized (1:1) to start either the mini-MED or Western dietary interventions, with subsequent assignment to the other upon completion of the first. A second randomization within the mini-MED arm is conducted to allocate participants to order of consumption of either salmon or lean, unprocessed beef as a protein source resulting in a total of four possible intervention orders (Fig. 1). Lean, unprocessed beef is consumed as the protein source in both Western intervention periods. A permuted block randomization scheme and stratification by sex has been generated and is utilized to ensure balance between intervention order and number of males and females. The allocation sequence was generated using computer-generated random number sequence in R using the *sample* command in *base* R package.

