## Statistical methods

### Statistical methods for primary and secondary outcomes {20a}

Assessment of the primary outcome of change in FSCs will be completed using the intercept of linear mixed effects models (LMMs) with change in FSCs (post–pre) as the outcome and a random intercept to control for repeated measures. Analysis will be stratified by mini-MED and Western interventions since we expect FSCs to increase during the mini-MED arm and to decrease during the Western arm. FSCs that significantly increase during the mini-MED interventions and significantly decrease during the Western interventions will be considered validated. We will adjust for multiple testing using false discovery rate (FDR) for the number of FSCs [37]. We will complete stratified analysis by intervention period to assess reproducibility of FSCs in increase (mini-MED) and decrease (Western). The relationship between cardiometabolic health indicators and diet intervention will be assessed using LMMs similar to that described above. The relationship between cardiometabolic health indicators and FSCs will be assessed using LMMs over all intervention periods with an interaction term for FSCs and diet (i.e., mini-MED, Western) to capture differential effects by diet.

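### The single validation rule runs in the wrong direction for beef compounds and weakens the test for salmon compounds

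*Protocol article*

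**What the plan says.** Statistical methods {20a} models the post-minus-pre change separately for the mini-MED and Western interventions, "since we expect FSCs to increase during the mini-MED arm and to decrease during the Western arm". The decision rule follows: "FSCs that significantly increase during the mini-MED interventions and significantly decrease during the Western interventions will be considered validated". It makes no exception by food.

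The Abstract defines the primary outcome over "FSCs from the eight MED target foods in participant biospecimens", and the eighth food is "a protein source (alternating between salmon or unprocessed, lean beef". Table 1 lists both salmon and beef as mini-MED target foods.

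On feeding, Sequence generation {16a} states: "Lean, unprocessed beef is consumed as the protein source in both Western intervention periods". Each participant gets one protein in the first mini-MED period, "with consumption of the alternate protein source in their second mini-MED intervention period" (Trial design {8}). The two randomizations give four sequences, "resulting in a total of four possible intervention orders".

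Objectives {7} includes in the primary hypothesis that FSCs respond to intake, "with beef FSCs stable and reproducible within the context of different dietary backgrounds".

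**The concern.** The rule treats mini-MED as the period when the food is eaten and Western as the period when it is not. That is true of seven foods. It is not true of beef, which is withheld only in the mini-MED salmon period, and it is only partly true of salmon, which is absent from one mini-MED period.

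If the rule is applied as written, good beef intake markers would be reported as not validated, and salmon markers would face a weaker test than the other foods for reasons of scheduling alone. The rule also gives no criterion for the beef hypothesis: a compound at the same level on both backgrounds neither rises in one nor falls in the other.

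**Working it through.** **Scope, from the protocol's own count.** Plasma compounds in Table 1 for the seven non-protein mini-MED foods: 30 + 136 + 27 + 112 + 23 + 17 + 10 = 355. This reproduces the 355 in Sample size {14}. Salmon (143) and beef (76) add 219, giving 574, so 219/574 = 38% of the listed mini-MED plasma compounds lie outside that count but inside the primary outcome as the Abstract defines it.

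**Expected changes.** Write S for mini-MED salmon, B for mini-MED beef and W for Western. The sequences are S-W-B-W, B-W-S-W, W-S-W-B and W-B-W-S. Let a compound be at level 1 after a period in which its food is provided and 0 otherwise. Each period's pre value is the preceding period's post value (Plans for assessment {18a}). With level 0 at baseline:

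| Sequence | Beef, mini-MED | Beef, Western | Salmon, mini-MED | Salmon, Western |
|---|---|---|---|---|
| S-W-B-W | 0, 0 | +1, 0 | +1, 0 | -1, 0 |
| B-W-S-W | +1, -1 | 0, +1 | 0, +1 | 0, -1 |
| W-S-W-B | -1, 0 | +1, +1 | +1, 0 | 0, -1 |
| W-B-W-S | 0, -1 | +1, 0 | 0, +1 | 0, 0 |
| Mean of 8 | -2/8 = -0.25 | +5/8 = +0.625 | +4/8 = +0.50 | -3/8 = -0.375 |

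The other seven foods give +8/8 = +1.00 and -6/8 = -0.75.

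Baseline intake is not controlled, so I repeated this with level 1 at baseline (mini-MED, then Western): beef -0.50 and +0.375; salmon +0.25 and -0.625; other foods +0.75 and -1.00. Beef has the wrong sign in both arms at either extreme.

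**Chance of meeting the joint rule.** Simulation with 20 participants (5 per sequence), SD of a change = 1, zero baseline, independent visit errors, and two-sided tests of the pooled mean change in each arm, with the variance estimated as in a random-intercept model (20,000 runs). Effect sizes 0.45 and 0.75 and the threshold 0.05/21 = 0.0024 come from Sample size {14}.

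| d | alpha | Other seven foods | Salmon | Beef |
|---|---|---|---|---|
| 0.45 | 0.05 | 0.45 | 0.10 | 0.0001 |
| 0.75 | 0.05 | 0.89 | 0.28 | 0.00 |
| 0.75 | 0.0024 | 0.41 | 0.02 | 0.00 |

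With a one-sample t-test on participant means instead, salmon at d = 0.75 and alpha 0.05 comes to 0.34, hence about 0.3.

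**Effect of food-specific periods for salmon.** Under that t-test, testing the rise over the salmon period (20 changes) and the fall over the following Western period (15 changes) raises the joint probability at d = 0.75 from 0.34 to about 0.72 at alpha 0.05, and from about 0.04 to 0.18 at alpha 0.0024.

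**The case against.** The strongest objection is that the rule was never meant for the protein foods. The Background introduces beef as an additional evaluation, Objectives {7} gives it its own expectation, and the 355 count leaves out both proteins. This has force: it shows an inconsistent scope rather than a settled decision to fail beef compounds. But the Abstract and section {20a} exclude neither food, and if exclusion was intended, {20a} then states no criterion for either.

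The planned analysis by intervention period does not rescue the rule. It is offered for reproducibility, still expects a Western decrease and is not said to be split by protein. Because protein order is randomized, each mini-MED period mixes salmon and beef eaters.

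A reader might go further in four ways that the documents do not support:

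- That nothing in the plan tests beef. The article may leave a beef model to an analysis plan that is not shown. What can be said is that {20a} states no criterion.
- That the reversed signs contradict the stability hypothesis. That hypothesis concerns beef across backgrounds when it is eaten; a fall while salmon replaces it is compatible with it.
- That most true salmon markers would be missed. This depends on effect size and threshold: at d = 1.0 and alpha 0.05 about 56% pass, and at d = 1.5 about 82%. At 0.0024 and d = 0.75 even the other foods pass only 41% of the time, which is a separate sample-size matter.
- That the non-salmon periods carry no salmon signal at all. That holds only with zero baseline and no carry-over; omnivorous participants may have eaten salmon before entry.

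Trial design {8} also calls the outcome assessment exploratory, and samples are batch-analysed at study completion. This makes the wording easier to correct, but a rule that labels compounds validated still has to point the right way.

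**Conclusion.** The point holds. For beef it is a matter of sign: an intake-tracking compound is expected to move against the rule in both arms, at zero or full baseline level, so a larger sample would not help and validation could occur only by chance. This needs only the feeding schedule, equal sequences and no carry-over; the simulation merely confirms it.

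For salmon it is a loss of power. The rule can be met, but the expected changes are half those of the other foods at zero baseline. With full baseline presence they are a third in mini-MED (0.25/0.75) and five-eighths in Western (0.625/1.00). The probabilities of about 0.3 against 0.9 are illustrative: they use a fixed alpha in place of the planned false discovery rate and do not model the rank transform in {20c}. Salmon alone would be a weakness; the beef reversal and the inconsistent scope make this something to correct before the data are analysed.

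**What to change.** Reconcile the Abstract, Objectives {7}, Sample size {14} and Statistical methods {20a} on which foods the rule covers, and define the tests by when each food was provided:

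- **Seven foods given in both mini-MED periods:** keep the current rule.
- **Salmon:** test the rise over the mini-MED salmon period and the fall over the Western period that follows it, with the mini-MED beef period as negative control.
- **Beef:** contrast levels after beef periods with levels after the mini-MED salmon period to show response to intake. For stability across backgrounds, report mini-MED beef minus Western beef with a confidence interval.
- **Multiplicity:** state whether salmon and beef compounds belong to the same false-discovery family.

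The cost is small. No new data or visits are needed. The salmon fall is available in three of four sequences, about 15 of 20 participants, because one sequence ends on salmon. The beef contrasts use end-of-period levels rather than the change outcome in Outcomes {12}, so they should be named as a stated addition to it.

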### Interventions

#### Explanation for the choice of comparators {6b}

As this is a multi-intervention design, each participant serves as his or her own control to evaluate the primary outcome of detection of FSCs in biospecimens after consumption of each dietary intervention and reproducibility over time within an individual.

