#### Intervention description {11a}

The dietary interventions are as follows: (1) Mediterranean-amplified (mini-MED) diet, containing 500 kcal/day from Mediterranean target foods: avocado, basil, cherry, chickpea, oat, red bell pepper, walnut, and salmon or lean, unprocessed beef as a protein source, and (2) habitual/Western (Western) diet, containing 500 kcal/day from non-Mediterranean target foods: cheesecake, chocolate frozen yogurt, refined grain bread, sour cream, white potato, and lean, unprocessed beef. Each intervention is 4 weeks, with a 2-week washout after enrollment but prior to initiation of the first dietary intervention (Fig. 1). Furthermore, each intervention is repeated to evaluate reproducibility within individuals over time.

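### The period-stratified mean-change analysis shows group-level replication, not the within-individual reproducibility in the primary hypothesis, and salmon is supplied only once per participant

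*Protocol article*

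**What the plan says.** Objectives {7} states the primary hypothesis that "pre-defined FSCs in participant biospecimens will be responsive to dietary intakes and reproducible within individuals over time". Explanation for the choice of comparators {6b} gives the purpose of comparing participants with themselves: "to evaluate the primary outcome of detection of FSCs in biospecimens after consumption of each dietary intervention and reproducibility over time within an individual". The reason for the repeat is found in Intervention description {11a}: "each intervention is repeated to evaluate reproducibility within individuals over time".

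In Statistical methods for primary and secondary outcomes {20a}, the main model is described as "using the intercept of linear mixed effects models (LMMs) with change in FSCs (post–pre) as the outcome and a random intercept to control for repeated" observations per person, and it is fitted separately for the mini-MED and Western diets. For reproducibility the same section names one analysis: "We will complete stratified analysis by intervention period to assess reproducibility of FSCs in increase (mini-MED) and decrease (Western").

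On salmon, Trial design {8} randomizes participants to salmon or beef in their first mini-MED period, "with consumption of the alternate protein source in their second mini-MED intervention period". Sequence generation {16a} adds: "Lean, unprocessed beef is consumed as the protein source in both Western intervention periods".

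**The concern.** The hypothesis is about individuals and the named analysis is about averages. Once the data are split by period, each person contributes one change score per stratum, and nothing in the stratum links it to that person's other response. A compound can rise on average in both periods while the size of a person's first response says nothing about the second.

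At stake is what the trial can claim about half of its primary hypothesis, and the return on repeating each diet. The rule by which a compound is declared validated in {20a} (an increase on mini-MED and a decrease on Western) is not affected.

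Salmon is a separate matter of design. The hypothesis covers all the pre-defined compounds without exception, but a participant receives salmon in only one of four periods. In Table 1 salmon has the largest number of compounds detected in plasma (143), so the gap is not marginal.

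**Working it through.** The article gives no figure for reproducibility, so there is none to reproduce. Its sample-size section supplies only the inputs below.

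**Inputs**
- Completers: n = 20 (Sample size {14}).
- Effect size: d = 0.75, mean change divided by SD of change, the median for salmon compounds passing the FDR threshold (Sample size {14}).
- Two mini-MED periods per participant (Sequence generation {16a}).
- Assumed here: two-sided 0.05 in each period, normally distributed change scores with equal means, and a correlation rho between a person's first and second change. The article analyses ranked values, so this is a simplification.

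**1. What a period stratum can estimate.** With one change score per person, the variance of the observations is (between-person variance + residual variance), and the two parts cannot be separated. The intercept is the group mean change. No within-person quantity is estimable inside the stratum.

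**2. Response of the strata to within-person consistency.** Suppose a compound is called reproducible when it is significant in both exposures.
- Power per exposure, paired t-test: noncentrality = 0.75 × √20 = 3.354, 19 df, critical t = 2.093, power = 0.889.
- rho = 0: the two tests are independent, so both are significant with probability 0.8888² = 0.790.
- rho = 0.6, by simulation: 0.82.
- rho = 0.9, by simulation: 0.85.

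Moving from no within-person correlation to a very strong one changes the pass rate from about 79% to about 85%.

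**3. What the data already planned could show.** For the seven foods given in both mini-MED periods (avocado, basil, cherry, chickpea, oat, red bell pepper, walnut), the pooled random-intercept model has two responses per person and yields an ICC. One-way 95% limits with n = 20, k = 2:
- F = (1 + ICC)/(1 − ICC); lower F_L = F / F₀.₉₇₅(19, 20); upper F_U = F × F₀.₉₇₅(20, 19); each limit = (F* − 1)/(F* + 1), with F* = F_L or F_U.
- ICC 0.6 (assumed): F = 1.6/0.4 = 4; F_L = 4/2.482 = 1.612; F_U = 4 × 2.509 = 10.04; interval 0.23 to 0.82.
- ICC 0.8 (assumed): F = 1.8/0.2 = 9; F_L = 3.626; F_U = 22.58; interval 0.57 to 0.92.

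**4. Why the ICC cannot stand alone.** With d = 2 and rho = 0, a person rises in one period with probability Φ(2) = 0.977, and in both with probability 0.977² = 0.955. The ICC is 0, yet 95.5% of people rise both times. The ICC measures whether differences between people persist, so it can be near zero when everyone responds alike.

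**5. Salmon.** Two mini-MED periods, one with salmon and one with beef; two Western periods, both with beef. That is one salmon response per person (k = 1), so no repeatability measure exists. Beef is supplied in three of the four periods.

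**The case against.** The best defence is that {20a} never says a compound must be significant in each period. The stratified analysis is a supporting step with no pass mark. That stands, and the 79% and 85% above are therefore illustrations under a stated reading.

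A reader might go further and infer that truly reproducible compounds would usually fail. With strata by calendar period, about 10 people per diet, power at d = 0.75 is 0.562, and at least one of two independent tests misses with probability 1 − 0.562² = 0.68. The documents do not support that figure as a property of the plan. It needs both the unstated rule and the less favourable meaning of period. Everyone completes each diet twice, so strata by first and second exposure have n = 20, and the same calculation gives 1 − 0.790 = 0.21.

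The defence can also say that the main model keeps both periods per person and that an analysis plan could report its variance component. The data are indeed retained. But the article assigns the random intercept only to handling repeated measures, and names a different analysis for reproducibility. The point is a method that does not match its purpose, not an omitted detail.

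Finally, Trial design {8} calls the outcome assessment exploratory, and the Discussion leaves reproducibility and interindividual variability to future studies. This tempers the severity but does not remove the wording of the hypothesis. On salmon, the alternation is openly described, repetition is true at the level of the diet, and no salmon-specific within-person claim is made. The general hypothesis still includes salmon.

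**Conclusion.** The concern holds in this form: the analysis named for reproducibility shows replication of the group mean and barely responds to consistency within a person (about 79% against 85% for correlations of 0 and 0.9). Those figures rest on n = 20, d = 0.75, normal change scores, first-versus-second-exposure strata and a both-significant reading at 0.05. The mismatch itself rests on none of them. It follows from one change score per person per stratum.

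For salmon, within-individual reproducibility cannot be estimated from the supplied exposures, whatever the analysis.

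Two stronger readings should not be drawn. One is that most reproducible compounds would be rejected, since that depends on a rule and strata the article does not fix. The other is that a low ICC would refute the hypothesis, since it can be low for a marker that rises in nearly everyone each time. The point should be addressed before analysis, because it changes what can be concluded about the primary hypothesis.

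**What to change.** In {20a}:
- Keep the stratified analysis, describe it as group-level replication, and define the strata as first versus second exposure to the diet (about 20 participants each).
- For the seven foods given in both mini-MED periods, add paired measures per compound: the proportion of participants whose compound rises in both periods; the mean difference between first and second response with its CI; and the within-person SD and the ICC with CI from the pooled random-intercept model.
- State that the ICC is read beside the other measures and is not the sole definition of reproducibility.
- State that salmon is supplied in one period per participant, so its compounds support a claim of responsiveness and no claim of within-individual reproducibility. Word the hypothesis in {7} and the statement about repetition in {11a} to match.

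The cost is analysis wording; no new data are needed. The downside is that ICC intervals at n = 20 are wide (0.23 to 0.82 for an ICC of 0.6) and the salmon claim becomes narrower.

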### Outcomes {12}

The primary outcome for this clinical trial is change in the relative abundance of FSCs from beginning to the end of each dietary intervention period in participant plasma samples. Secondary outcomes include detection of FSCs in participant urine samples as well as mean changes in cardiometabolic health indicators (e.g., total cholesterol, LDL cholesterol, HDL cholesterol, triglycerides, insulin, glucose, systolic and diastolic blood pressure), inflammatory markers (e.g., C-reactive protein, interleukin-6, tumor necrosis factor-alpha, alpha-1-acid glycoprotein), and adipokines (e.g., leptin, adiponectin) over each dietary intervention. Exploratory outcomes include changes in diversity and community composition of the gut microbiota over each dietary intervention period.

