### Data collection and management

#### Plans for assessment and collection of outcomes {18a}

As described above, during the eligibility/enrollment visit at the CTRC, participants complete informed consent and Health Insurance Portability and Accountability Act (HIPAA) authorization via the e-Consent framework in REDCap [23]. Those deemed eligible are provided materials by mail for at-home biospecimen sampling, including 24-h and spot urine collection containers, fecal collection kits, and items needed to transport the biospecimens to subsequent study visits for drop off. Future visits are also scheduled at this time. Participants complete data collection visits pre- and post- each dietary intervention period for a total of six in-person assessments (including eligibility/enrollment) over the duration of the 16-week intervention. The samples obtained and procedures conducted at intervention weeks 4, 8, and 12 will generate data that serve as both post-intervention data for the respective preceding intervention and pre-intervention data for the respective ensuing intervention. Mid-intervention phone calls with the study coordinator are conducted for each intervention period. Outcomes are assessed via standardized, self-report questionnaires that can be completed remotely or in-person at assessments at the CTRC as outlined below. Participants also complete several biospecimen collections throughout the study. Prior to each data collection visit, participants are asked to fast overnight (consume nothing except for water for a minimum of 12 h), to drink plenty of water the day before and morning of the visit, and to abstain from vigorous exercise and alcohol consumption for 48 h prior to the scheduled visit. Details regarding the sampling plan and data collection at each time point are outlined in Table 3.

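### For the cardiometabolic, inflammatory and adipokine outcomes, the model pointed to tests change within each diet, while the hypothesis also asks for mini-MED compared with Western

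*Protocol article*

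**What the plan says.** Objectives {7} sets the secondary hypothesis for cardiometabolic indicators and the gut microbiome as improvement "over time and compared to a habitual/Western-style dietary pattern". Outcomes {12} defines the secondary outcome as "mean changes in cardiometabolic health indicators", inflammatory markers and adipokines over each dietary intervention.

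Statistical methods {20a} describes the primary analysis in full. It "will be completed using the intercept of linear mixed effects models (LMMs) with change in FSCs" as the outcome, and "Analysis will be stratified by mini-MED and Western interventions". For diet and the cardiometabolic indicators the section then says only: "The relationship between cardiometabolic health indicators and diet intervention will be assessed using LMMs similar to that described above".

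One other cardiometabolic model in that section mentions diet. It relates the indicators to food-specific compounds (FSCs), "with an interaction term for FSCs and diet (i.e., mini-MED, Western) to capture differential effects by diet".

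Plans for assessment {18a} states that the week 4, 8 and 12 samples "serve as both post-intervention data for the respective preceding intervention and pre-intervention data for the respective ensuing intervention". Sequence generation {16a} randomises the order of the diets 1:1, and every participant takes each diet twice.

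**The concern.** A model fitted within one diet has no diet coefficient. Its intercept tests whether mean change on that diet is zero. Lipids, blood pressure, glucose, inflammatory markers and adipokines would each receive two such tests and no estimate of how the diets differ. A result that is significant on mini-MED and not on Western is not evidence of a difference between them.

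A within-diet change also contains whatever else moved over those four weeks: season, familiarity with the visits, behaviour on joining a study, assay drift. The randomised order allows drift to be separated from diet, but a diet-stratified intercept makes no use of it.

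**Working it through.** **1. Do the passages match?** The hypothesis has two parts, over time and compared with Western. The intercept of change, by diet, addresses the first. The FSC-by-diet interaction asks whether the FSC–indicator slope differs by diet, which is not the effect of diet on the indicator. The second paragraph of {20a} names between-group tests (negative binomial mixed models, PERMANOVA), but for microbiota only. No passage states a mini-MED minus Western estimate for the cardiometabolic, inflammatory or adipokine outcomes. The plan gives no power figure for this hypothesis, so there is none to reproduce.

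**2. Effect of a time trend on the stated test.** From the plan: 20 completers, visits y0 to y4 (weeks 0, 4, 8, 12, 16), alternating diets. Assumed: 10 participants per starting order, independent visit noise with SD 1 around each person's level, no diet effect, no dropout, two-sided 5%.
- Mini-MED-first: a participant's mean mini-MED change is [(y1 − y0) + (y3 − y2)]/2, with variance 4/4 = 1 and expectation b for a drift of b per period. Western-first gives the same variance and expectation.
- The test is then a one-sample t with 19 df and non-centrality b√20: 1.118 at b = 0.25 and 2.236 at b = 0.5.
- Rejection is about 19% and 56%. Simulation (20,000 runs) gave 5.1%, 18.9% and 56.4% at b = 0, 0.25 and 0.5.
- In the same runs exactly one diet was significant in 7%, 37% and 70%. A direct within-person mini-MED minus Western contrast stayed at 5%.

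**3. Two obvious repairs that go wrong.**

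*(a) Subtracting the two mean changes.* Suppose Western holds participants at baseline and mini-MED shifts the end-of-period value by d.
- Mini-MED-first (y = 0, d, 0, d, 0): mean mini-MED change is d, mean Western change is −d, difference 2d.
- Western-first (y = 0, 0, d, 0, d): mean mini-MED change is d, mean Western change is (0 − d)/2 = −0.5d, difference 1.5d.
- Average: (2d + 1.5d)/2 = 1.75d. The test of no difference stays valid, but the estimate is not the diet difference.

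*(b) Pooling the four changes with a diet term and only a random intercept.*
- For mini-MED-first the contrast of mean changes is (−y0 + 2y1 − 2y2 + 2y3 − y4)/2, with variance (1 + 4 + 4 + 4 + 1)/4 = 14/4. Western-first is the same with signs reversed.
- A model that treats the four changes (variance 2 each) as independent assigns 8/4. The ratio is 14/8 = 1.75, equal to the factor in (a) by coincidence.
- A nominal 5% test then has error 2 × [1 − Φ(1.96/√1.75)] = 2 × [1 − Φ(1.48)], about 14%. A random intercept cannot absorb the negative correlation between adjacent changes that share a visit.

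**4. The end-of-period contrast.** For mini-MED-first, (y1 + y3)/2 − (y2 + y4)/2 has expectation d − b; for Western-first the mini-MED minus Western contrast has expectation d + b. Averaged over equal orders, or with period in the model, drift cancels and d is recovered. Fitting the mixed model proposed under the fix to simulated data (600 runs, person SD 1, drift 0.5) gave a mean estimate of 0.59 for a true 0.60. With no diet effect and a normal reference distribution it rejected in about 7% of runs (Monte Carlo error about 1 point), so a small-sample degrees-of-freedom method is worth naming.

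**The case against.** The strongest reply is that the sentence calls the models similar, not identical, and speaks of a relationship with diet, which could imply diet as a predictor. The stated reason for stratifying concerns the expected direction of the FSCs and need not extend to lipids or blood pressure. A separate analysis plan might settle it. This stands to the extent that a reader might infer that the plan rules out a diet contrast; it does not. The text simply points to a model without one.

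A reader might also infer that the whole secondary hypothesis goes untested. That is too broad: the over-time half is tested, and the microbiota outcomes have between-group tests.

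Three of every four mini-MED changes start from the end of a Western period (both for Western-first, the second for mini-MED-first), so they carry a within-person diet difference. True, but it is confounded with time. The rule requiring a rise on mini-MED and a fall on Western does resist drift: with no diet effect, simulated opposite-direction significance was 1.8% without drift and at most 0.3% with drift of 0.25 to 0.5 SD per period. That rule is written for FSCs only.

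Finally, end-of-period values are not the outcome named in Outcomes {12}. That is fair, and is why the within-diet mean changes should stay alongside the contrast.

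**Conclusion.** The point holds for the cardiometabolic, inflammatory and adipokine outcomes, and for the comparative half of the hypothesis only. Followed as written, {20a} gives no mini-MED minus Western estimate, and its within-diet tests cannot separate diet from time.

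The 19% and 56% depend on assumed drifts of 0.25 and 0.5 SD per period and on independent visit noise. The documents give no drift or variance for these indicators; without drift the error is the nominal 5%.

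The 1.75 factor and the 14% error are not faults in the plan's text, though a reader might take them so. They describe repairs that the plan does not state and that should be avoided. Nor should one infer that, at 50% power per diet, exactly one diet would be significant half the time: that assumes independent strata, and shared visits make these negatively correlated.

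Severity is should-fix. The outcomes are secondary, Trial design {8} describes the assessment as exploratory, and the primary outcome and data collection are unaffected.

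**What to change.** In {20a}, replace the sentence on cardiometabolic indicators and diet with a stated model. For each cardiometabolic, inflammatory and adipokine outcome, fit one linear mixed model to the values at weeks 4, 8, 12 and 16, with:
- diet and period as fixed effects, and sequence if wanted;
- the week-0 value as covariate;
- a random participant intercept;
- a small-sample degrees-of-freedom method.

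Report mini-MED minus Western with a 95% CI as the test of the comparative hypothesis. Keep the within-diet mean changes of Outcomes {12} as the over-time summary. Say that the contrast is not obtained by subtracting mean changes, nor by adding a diet term to pooled changes with only a random intercept.

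The contrast takes carry-over between periods as negligible. The retention section {18b} already regards four weeks of Western as enough for metabolic status to return to baseline, so that assumption can be stated with the model.

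The cost is a short change of wording and one added estimand. No new data are needed, and samples are to be batch-analysed at study completion, so the model can be fixed before those results exist.
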